#### Statistical Methods and Power

##### Aim 1: Examine differences between TBI and OI in BDNF methylation and BDNF protein levels over the recovery period

Unadjusted *BDNF* methylation and protein levels will be compared between TBI and OI groups using mixed effects analysis of variance (ANOVA; time as within effect; group as between effect). Mixed effects ANOVA allows for the modeling of effects on continuous outcomes (BDNF methylation and protein levels), is flexible with missing data, and provides explicit estimation of between group and within group variance. We will use appropriate transformations if normality is violated. We expect a significant group × time interaction and group differences at each time point. Alpha will be set at 0.05, and we will adjust for multiple comparisons using Bonferroni corrections. We expect sufficient power (≥0.8) to detect even a small interaction effect (partial η^2^ = 0.01) assuming correlation of 0.5 between repeated measures (G^*^Power 3.1.9.2).

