### Biomarker Collection and Processing

CSF is collected by the bedside nurse into a CSF vial and refrigerated until processing within 48 h by the CHP PCTRC. Processing involves separation and aliquoting of supernatant for future protein level analysis and the cell pellet for genetic and epigenetic analysis. Processed samples are stored at −80°C.

Acute blood samples are collected by the child's bedside nurse from his or her IV if patent or via venipuncture with parent and child permission. Chronic blood samples are collected via venipuncture by a PCTRC nurse. Up to 10 cc of blood is collected at each draw into ethylenediaminetetraacetic acid (EDTA) vacuum tubes and refrigerated until processing within 48 h by the PCTRC. Processing involves separation and aliquoting of plasma for future protein level analysis and the buffy coat (leukocytes) for DNA extraction using a simple salting protocol for genetic and epigenetic analysis. Processed samples are stored at −80°C.

Up to 2 ml of saliva is collected by the study staff using Oragene DNA sample collection kits (DNA Genotek, Ontario, Canada). To collect saliva, the child spits into the Oragene collection tube for 2–5 min until liquid saliva reaches the fill line. If the child is unconscious or unable to spit, study staff instead use a sponge to gently swab the child's gums and inner cheeks and then wring the saliva out of the sponge into the collection tube until the fill line is reached. The study staff then close the tube's lid to release the stabilizing liquid and store the sample at ambient temperature until processing. DNA is extracted using the reagents and protocol from the manufacturer.

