### Potential Covariates/Confounds

*BDNF* methylation and protein levels vary by age, sex, and pubertal status (98–101), as well as lifestyle factors including BMI and smoking (101–103); therefore, we are collecting information on these factors at all time points to be investigated as potential covariates. We will also examine the effect of overall bodily injury severity because polytrauma can be a significant confounder in biomarker studies (75, 104).

Pubertal status is measured for children ≥8 years using the self-report Pubertal Development Scale (105). The scale provides a Pubertal Development Score, which shows adequate agreement with direct clinical assessment of Tanner staging (106).

The child's BMI is obtained at each visit from the EMR or study staff.

Parents are given a brief screener measuring the child's exposure to nicotine and tobacco. The screener measures maternal use and secondhand exposure during pregnancy, as well as the child's secondhand exposure. Children 10 and up also complete a brief self-report measure about their own nicotine and tobacco use. They are asked how frequently they have used a variety of nicotine/tobacco products. Children complete the questionnaire on paper while their parents are out of the room and are informed that their responses will be kept private.

The Injury Severity Score (ISS) (107) measures overall bodily injury severity and is obtained from the local trauma registry. The score for injury to the head will be excluded to avoid confounding with TBI severity.

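### Aim 1 fixes an unadjusted TBI-versus-OI biomarker comparison, although the protocol names and collects the likely confounders; the differences at each visit are most exposed

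*Protocol article*

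**What the plan says.** The Aim 1 paragraph of Statistical Methods and Power sets the comparison as "Unadjusted *BDNF* methylation and protein levels will be compared between TBI and OI groups", by a mixed effects ANOVA with the terms given as "time as within effect; group as between effect". It expects both a group x time interaction and a group difference at every time point. On error control it says "Alpha will be set at 0.05, and we will adjust for multiple comparisons using Bonferroni corrections".

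Potential Covariates/Confounds says that BDNF "methylation and protein levels vary by age, sex, and pubertal status", adds BMI and smoking, and warns that "polytrauma can be a significant confounder in biomarker studies". These factors are collected at all time points. The Injury Severity Score (ISS) is taken from the trauma registry with the head score left out.

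Study Overview describes consecutive overnight admissions at one hospital and mentions no matching. It gives the OI group the task of helping to separate general injury effects on systemic biomarkers from brain-specific ones. Under Inclusion Criteria, every OI child has a fracture outside the skull and face. Under Exclusion Criteria, a TBI child may or may not also have an orthopedic injury.

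**The concern.** The protocol identifies what moves the biomarker apart from brain injury, measures it, and then leaves it out of the one analysis that compares the two injury groups. Covariates enter the Aim 2 latent class models, which are fitted to children with TBI, and the Aim 3 path analysis, which is also within TBI. Neither contrasts TBI with OI.

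If the groups differ in age, sex, BMI or tobacco exposure, part of any TBI-OI difference at a visit may reflect those factors. Extracranial injury is the sharpest case, because the eligibility rules themselves make the groups differ on it. The inference at stake is the one for which the OI group was chosen. The results are also meant to guide a larger multisite study, so a misattributed difference could carry forward.

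**Working it through.** **1. Which analyses compare TBI with OI?**

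| Analysis | Children | Covariates |
|---|---|---|
| Aim 1, mixed ANOVA | TBI and OI | none (labelled unadjusted) |
| Aim 2, latent class trajectories | TBI only | age, sex, puberty, TBI severity, overall injury severity, BMI, smoking |
| Aim 3, path analysis | TBI only | Aim 2 covariates through the trajectory classes; premorbid function (except for the NIHTB-CB) |

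The only row with both groups has no covariates.

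**2. The protocol's own power figure.** Inputs from Aim 1: partial eta-squared 0.01, correlation 0.5, alpha 0.05. There are three visits, and Data Reduction, Missing Data, and Attrition expects 150 TBI and 75 OI children at follow-up (N = 225). Under the G*Power default convention:

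- f² = 0.01/0.99 = 0.0101
- lambda = f² x N x 3/(1 − 0.5) = 0.0101 x 225 x 6 = 13.64, with 2 and 446 degrees of freedom
- power = 0.919 (0.975 at N = 300)

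The stated power of at least 0.8 is reproduced.

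**3. Which Aim 1 contrast does a confounder reach?** A time-fixed confounder with a constant effect adds the same shift to the group difference at each visit. That shift cancels from group x time but stays in full in each per-visit difference. An effect that changes over time does not cancel. Extracranial injury may act this way, being largest acutely and then fading; this is a plausible assumption, not something the protocol states.

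**4. Size at one visit.** The protocol gives neither the imbalance nor the correlations, so these inputs are assumed: an age gap of 1.5 to 2 years, an age SD of 4.5 years, and an age-biomarker correlation of 0.3 to 0.4.

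- Bias in SD units = correlation x gap/SD
- Low: 0.3 x 1.5/4.5 = 0.10
- High: 0.4 x 2/4.5 = 0.18
- Standard error of the group difference = sqrt(1/150 + 1/75) = 0.141 SD
- With no true difference, false-positive rate = Φ(bias/SE − 1.96) + Φ(−bias/SE − 1.96)
- Bias 0.10: bias/SE = 0.71, rate 0.109
- Bias 0.18: bias/SE = 1.27, rate 0.247

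Over a wider assumed grid at nominal 0.05:

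| Confounder imbalance (SD) | Correlation with biomarker | Bias (SD) | False-positive rate |
|---|---|---|---|
| 0.2 | 0.2 | 0.04 | 0.059 |
| 0.3 | 0.3 | 0.09 | 0.098 |
| 0.5 | 0.3 | 0.15 | 0.186 |
| 0.5 | 0.5 | 0.25 | 0.424 |

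If Bonferroni is taken over three visits (0.0167 each; the protocol does not give the number of comparisons), the four rates are 0.021, 0.041, 0.091 and 0.266. The correction lowers the threshold but leaves the bias in place.

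**5. Cost of adjusting.** Six covariates with their time interactions reduce the error degrees of freedom from 446 to 2 x (225 − 2 − 6) = 434. Interaction power stays at 0.919, with no credit for variance explained.

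**The case against.** The study calls itself an exploratory pilot. Its primary hypothesis concerns mediation of childhood adversity, tested with covariates in Aim 3. The OI group is already a design-level control for injury risk and the experience of trauma, and the protocol claims only that the comparison will help to separate effects. All this stands, and it lowers the weight of the point. It does not remove the difference in extracranial injury or justify labelling the sole group comparison unadjusted.

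The protocol also says that it will examine overall bodily injury severity, and that demographic and injury factors will be explored as covariates. Neither statement is limited to TBI, but neither is tied to Aim 1, whose model is spelled out. This is a stated choice, not a detail left to an analysis plan.

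Three stronger readings are tempting, and the documents do not support them:

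- **That the bias could equal the powered interaction effect.** A constant shift cancels from the interaction. Moreover, for group differences of +d, 0 and −d over the three visits, lambda = (2d²)(150 x 75/225)/(1 − 0.5) = 200d². The convention that reproduces the stated power therefore gives d = sqrt(13.64/200) = 0.26 SD, above the assumed 0.10 to 0.18. A value near 0.15 SD comes only from the literal reading of partial eta-squared, under which power at N = 225 would be 0.46.
- **That sponge collection of saliva occurs only in TBI.** The text reads "If the child is unconscious or unable to spit, study staff instead use a sponge". Inability to spit can occur in either group from age 3, and saliva may not be the biosample chosen for methylation.
- **That leaving out covariates wastes precision.** Baseline covariates mainly absorb between-child variance, which is not the error term of the interaction test.

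**Conclusion.** The point holds for the Aim 1 contrast as written. It bears chiefly on the hypothesised group differences at each time point and on the brain-specific inference. The interaction is exposed only to confounders whose effect changes over time, of which extracranial injury is the plausible one.

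The size cannot be computed from the protocol. With an assumed spurious difference of 0.10 to 0.18 SD, the per-visit false-positive rate at 150 vs 75 is about 0.11 to 0.25 instead of 0.05. For scale, the difference detectable with 80% power at one visit is (1.96 + 0.84) x 0.141 = 0.40 SD. A small imbalance would do little harm. For an exploratory pilot this should be fixed, but it does not invalidate the study.

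**What to change.** Keep the unadjusted mixed ANOVA as a descriptive analysis. Prespecify, as the basis for Aim 1 conclusions, a linear mixed model with group, visit, group x visit and baseline age, sex, BMI and tobacco exposure. Take tobacco exposure from the caregiver screener, which covers all ages; the child's own report starts at age 10. Age and sex are more practical than the pubertal score, which exists only from age 8.

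Treat extracranial injury separately, because the groups differ on it by definition and adjustment could rest on extrapolation. First compare the distribution of non-head ISS between the groups. Where they overlap, fit a further model that adds it. As a sensitivity analysis, compare TBI children who also have an extracranial fracture with the OI group.

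The cost is analysis wording and a few degrees of freedom: interaction power remains about 0.92 at N = 225 and alpha 0.05 under the G*Power default convention. The covariates named here are already collected.

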The BDNF pathway is also involved in neural recovery from TBI. BDNF is upregulated in the frontal cortex and the hippocampus after experimental TBI and may mediate recovery processes after brain injury (61–63). In adult clinical studies, BDNF levels in cerebrospinal fluid (CSF) show a sharp spike within 24 h postinjury and steadily decline over 1 week (64, 65), providing evidence for BDNF upregulation and involvement in recovery post-TBI consistent with animal models. BDNF levels during the first week postinjury tend to be comparable in CSF (65) but lower in serum in adults with TBI relative to nonbrain-injured controls (65, 66). Furthermore, acute and chronic BDNF levels in CSF and serum/plasma after TBI in adults predict outcomes, including mortality (65), global outcomes (66, 67), and long-term functional cognition and depression (68, 69). Far fewer studies have examined BDNF levels after pediatric TBI. Initial evidence shows a sharp peak in BDNF levels immediately following injury, followed by subsequent declines (70, 71), similar to that shown in adults. Higher CSF and plasma/serum BDNF levels predicted better global recovery in pediatric TBI studies (71, 72), but to our knowledge, no known studies have examined *BDNF* genetics or epigenetics in association with TBI outcomes in children.

Thus, the overarching goal of our study is to investigate an epigenetic biomarker involved in both childhood adversity and postinjury neuroplasticity to better understand heterogeneity in neurobehavioral outcomes following TBI. Our primary hypothesis is that childhood adversity will be associated with worse neurobehavioral recovery in part through an epigenetically mediated reduction in *BDNF* expression in response to TBI (see Figure 1).

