### Exclusion Criteria

Children in both the TBI and OI groups meet the following exclusion criteria: (a) non-English-speaking child or non-English-speaking parents/guardians; (b) documented or parent-reported history of previous TBI/concussion requiring overnight hospitalization; (c) preinjury neurological disorder or intellectual disability; (d) preinjury psychiatric disorder requiring hospitalization; (e) spinal cord injury; (f) sensory or motor impairment precluding study measure completion; and (g) pregnancy at the time of study participation. Participants are also excluded if at least one biosample is not able to be collected within 7 days of the injury. Children in the TBI group are not excluded if they also have an OI.

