For children and families who consent to study participation, an additional postconsent blood sample is obtained by the bedside nurse in addition to any preconsent acute blood and CSF samples. The study staff collect a saliva sample from the child. Prior to discharge, parents complete measures pertaining to demographic information, premorbid child functioning, childhood adversity, child resilience, and the child's pre- and postnatal exposure to nicotine/tobacco. Children 8 years and older complete a self-report measure of puberty status, and children 10 years and older also complete a self-report measure of tobacco/nicotine use. Injury information (e.g., mechanism, neuroimaging results, GCS) and BMI are obtained from the child's EMR.

The study staff contact families to schedule their 6- and 12-month follow-up research visits at CHP. Follow-up visits last ~90 min. At each visit, PCTRC research nurses collect blood via venipuncture, and the study staff collect saliva. Parents complete the same measures as the acute visit, this time to assess postinjury functioning (see Table 1 and Section Measures). Children complete the National Institutes of Health Toolbox-Cognition Battery (NIHTB-CB) and self-report measures of puberty and tobacco/nicotine use. Families who refuse to return for follow-up research visits are given the option to return parent study measures and the child saliva sample via mail. Families are provided with instructions for how to collect the saliva sample and complete the parent measures as well as return packaging and postage.

**Table 1 T1:** Study measures organized by domain, source of data, and assessment occasion.

**Domain/measures**	**Source/reporter**	**Parent/child time to complete (min)**	**Acute (preconsent)**	**Acute (postconsent)**	**6 months**	**12 months**

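### Aim 1 treats any blood draw from the first 7 days as one acute level and leaves out time from injury to draw, so the acute BDNF protein comparison may partly reflect draw timing

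*Protocol article*

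**What the plan says.** All references are to the protocol article.

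- **Model.** Aim 1 under Statistical Methods and Power compares unadjusted methylation and protein levels between TBI and OI, with "time as within effect; group as between effect". The three time levels are acute, 6 months and 12 months.
- **Window.** Under Exclusion Criteria, a child is excluded "if at least one biosample is not able to be collected within 7 days of the injury". Study Procedures likewise takes the acute sampling window as one week.
- **Expected course.** The Introduction says that BDNF levels in adult CSF "show a sharp spike within 24 h postinjury and steadily decline over 1 week". For children it reports an early peak followed by declines, without naming the fluid or the time scale.
- **Draw routes.** Under Study Procedures, a potentially eligible child in the PICU has blood taken before consent, together with a clinical draw. Children with more severe injuries are the ones sometimes housed there. Ward children are approached during the first week and sampled only after consent. For families who consent, "an additional postconsent blood sample is obtained by the bedside nurse in addition to any preconsent acute blood and CSF samples".
- **Covariates.** The Aim 2 list has age, sex, pubertal status, TBI severity, overall injury severity, BMI and smoking. Neither that list nor Potential Covariates/Confounds includes time from injury to draw. Injury Information does record the date and time of injury.

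**The concern.** The acute level pools a week during which, on the plan's own account, BDNF protein is moving. If draw times were spread alike in every subgroup, pooling would only add noise. The draw routes give reason to doubt that. A preconsent PICU sample can be taken as soon as clinical blood is drawn, whereas a ward sample waits for approach and consent. A consenting child from the PICU then has two acute blood values for one acute level.

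OI children must have no sign of head injury and no GCS below 15 (Inclusion Criteria), so the PICU route probably falls mainly to the TBI group. That is an inference; no draw times are given.

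Aim 1 hypothesises lower protein in TBI than in OI at all time points, and a rise over time in TBI. Both statements depend on the acute TBI mean. The Aim 2 trajectory classes start from the same acute value, and Aim 3 uses those classes as mediators. A difference in draw time could therefore pass into all three aims.

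**Working it through.** **Inputs from the article**
- "Alpha will be set at 0.05"; target effect "partial η^2^ = 0.01"; power stated "assuming correlation of 0.5 between repeated measures" (Aim 1).
- 150 TBI and 75 OI children at follow-up, N = 225 (Data Reduction, Missing Data, and Attrition).
- Three time points, two groups, acute window of 7 days.

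**Step 1: the plan's power figure.** The article says "We expect sufficient power (≥0.8) to detect even a small interaction effect". With the G*Power default for a within-between interaction:
- f² = 0.01/0.99 = 0.0101
- λ = f² × N × m/(1 − ρ) = 0.0101 × 225 × 3/0.5 = 13.64
- df = 2 and 2 × (225 − 2) = 446; power = 0.92

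The stated power of at least 0.80 reproduces and is not in dispute.

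**Step 2: the powered effect in SD units.** For TBI-OI differences over the three visits, λ = (150 × 75/225) × S/(1 − ρ) = 50 × S/0.5 = 100 × S, where S is the sum of squared differences about their mean.
- Differences +d, 0, −d at the three visits: S = 2d², so 200d² = 13.64 and d = 0.26 SD.
- A difference b at the acute visit only: S = (2/3)b², so 66.7b² = 13.64 and b = 0.45 SD.

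**Step 3: shift caused by draw time.** The documents give neither a plasma slope nor a draw-day distribution. Assume a linear fall of D SD over 7 days, the same in both groups. Shift in the acute contrast = (D/7) × difference in mean draw day.

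| Assumed fall D (SD) | 1 day apart | 2 days apart |
|---|---|---|
| 0.5 | 0.07 SD | 0.14 SD |
| 1 | 0.14 SD | 0.29 SD |
| 2 | 0.29 SD | 0.57 SD |

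**Step 4: effect on the interaction test.** With no true group effect, a shift b at the acute visit gives λ = 66.7b², and the nominal 0.05 test rejects as follows.

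| Shift b (SD) | λ | Rejection rate |
|---|---|---|
| 0.07 | 0.33 | about 0.08 |
| 0.14 | 1.31 | 0.16 |
| 0.29 | 5.61 | 0.55 |
| 0.57 | 21.66 | 0.99 |

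**Step 5: simulation.** There were 2,000 replicates per setting, with 150 and 75 children, ρ = 0.5 and no true group effect.
- With equal draw timing, the error rate was 0.04 to 0.05 whatever the fall.
- With mean draw times 1.4 days apart, it was 0.11, 0.26 and 0.73 for D = 0.5, 1 and 2.
- Across all settings, adjusting the acute value for days since injury brought the bias to 0.01 SD or less and the error rate to about 0.05 to 0.09. The remaining excess comes from the crude two-step adjustment used in the simulation.

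**The case against.** **The kinetics are borrowed.** The 24-hour spike and one-week decline are stated for adult CSF, but Biomarker Analysis assays plasma. For blood, the Introduction says only that first-week serum levels in adults are lower in TBI than in controls, and gives no slope. No first-week course is given for methylation. This stands, and it confines the firm part of the point to protein.

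**No difference in draw time is shown.** Children with more severe injuries are only sometimes in the PICU, and the preconsent route is open to any potentially eligible child there, including one with OI. This also stands: a difference by severity is plausible from the procedures, and a difference by group is an inference.

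**A stronger reading is tempting.** A reader might infer that the choice between the two PICU samples could reverse the sign of the hypothesised rise in protein. The documents do not support that, because they give neither the share of children with two samples, nor the gap between draws, nor the slope. The direction of any bias is not fixed either: early PICU draws would raise the TBI acute mean if levels fall over the week, and late post-consent draws would lower it.

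**Partly covered, or left to a fuller document.** TBI severity and overall injury severity are candidate covariates in Aim 2 and may absorb some of the timing difference there. They do nothing in Aim 1. Which of two acute samples enters the model could reasonably be left to a fuller plan. The model itself is not left open: the article calls it unadjusted and lists the covariates. The exploratory pilot label lowers the stakes but does not remove a possible bias.

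**Conclusion.** The point holds as a possible bias that the stated analysis does not control. It concerns mainly the acute plasma protein contrast, the group-by-time interaction for protein and the protein trajectory classes. For methylation it is only a caution.

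Its size cannot be fixed from the documents. For an assumed fall of 0.5 to 2 SD over 7 days, linear and equal in both groups, each day of difference in mean draw time moves the acute contrast by 0.07 to 0.29 SD. The lower end is small against the powered 0.26 or 0.45 SD. At the upper end, one day exceeds the first of these, and two days (0.57 SD) exceed both. If only TBI levels fall, this formula does not apply, and the TBI acute mean depends on the mix of draw days in that group.

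The plan should be changed: the weakness lies in a stated modelling choice, and the remedy is cheap.

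**What to change.** 1. Use one acute-sample rule for both groups that aligns draw time, for example the sample nearest a fixed time after injury. Taking the first sample obtained would be a poor rule: it would tend to select preconsent draws in the PICU and later post-consent draws on the ward, and could widen the imbalance.
2. Add time from injury to draw, acting at the acute visit only, to the Aim 1 model. Let its slope differ by group, and read the acute group contrast at a stated time after injury.
3. Add the same term to the Aim 2 trajectory model, so that the classes passed to Aim 3 are less dependent on draw time.
4. Report the distribution of draw time by group and by TBI severity.

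The cost is a few degrees of freedom and a change of wording. If draw times exist, no new data collection is needed. The article mentions only the date and time of injury, so the sponsor must confirm that sample draw times are recorded.

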**Figure 1 F1:**
[figure not shown]
Heuristic model of our primary hypothesis. **(A)** Children with greater childhood adversity may have higher pre-TBI *BDNF* methylation, which may lead to **(B)** higher *BDNF* methylation and lower BDNF protein levels in response to TBI and over the recovery period, resulting in lower neuroplasticity and worse neurobehavioral outcomes. **(C)** This pathway may contribute to a biological explanation for the association between greater childhood adversity and worse neurobehavioral outcomes following pediatric TBI. BDNF, brain-derived neurotrophic factor; OI, orthopedic injury; TBI, traumatic brain injury.

The study uses an observational, prospective, longitudinal concurrent cohort design to examine the epigenetic influence of the biologically relevant *BDNF* pathway on neurobehavioral recovery in 200 children with nonpenetrating complicated mild to severe TBI relative to 100 children with orthopedic injury (OI) but no brain injury at three time points (acute, 6 months, 12 months) during the first year of recovery. As one of the first studies of epigenetic effects in pediatric TBI, this is an exploratory pilot study. The study will establish a longitudinal biorepository that is innovative in its integration of acute and chronic biological samples with comprehensive data characterizing preinjury childhood adversity and postinjury neurobehavioral functioning. Only a portion of each biosample will be used for the analyses proposed in the present study; the remaining biosamples will be stored in the biorepository. This rich biorepository will be expanded longitudinally in subsequent studies and will provide opportunities to evaluate other epigenetic, genetic, and protein biomarkers and biological mechanisms in future secondary analyses. The results of the present pilot study will guide the design of a subsequent larger multisite study that will be sufficiently powered to examine additional epigenetic biomarkers while controlling for additional sources of heterogeneity in outcomes.

Our specific aims and hypotheses are as follows:

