Aim 1: Examine differences between TBI and OI in *BDNF* methylation and BDNF protein levels over the recovery period. We hypothesize that *BDNF* methylation will be higher, and BDNF protein levels will be lower, in children with TBI relative to OI at all time points, and that *BDNF* methylation will decrease, and BDNF protein levels will increase, in the TBI group over time but will remain relatively stable in the OI group.Aim 2: Characterize trajectory classes of *BDNF* methylation and BDNF protein levels following TBI while controlling for potential demographic, injury, and lifestyle covariates. We hypothesize the presence of at least two *BDNF* methylation trajectory classes and two BDNF protein level trajectory classes representing varying degrees of recovery from TBI. We will explore age, sex, pubertal status, TBI severity, overall injury severity, body mass index (BMI), and smoking as potential covariates.Aim 3: Test the indirect effect of childhood adversity on neurobehavioral recovery following pediatric TBI, as mediated by *BDNF* methylation and BDNF protein level trajectory classes.

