## Methods and Analysis

### Study Overview

Children aged 3–18 years with either complicated mild to severe nonpenetrating TBI (*n* = 200) or OI (*n* = 100) are recruited from consecutive overnight admissions to the UPMC Children's Hospital of Pittsburgh (CHP). The sample size of 200 children with TBI and 100 children with OI was chosen based on two considerations: (1) feasibility of recruitment over the study period based on historic numbers of children with TBI meeting eligibility criteria at our site and (2) adequacy of statistical power for proposed analyses taking into consideration participant attrition over the study period (see section Statistical Methods and Power). We selected the age and severity ranges to optimize sample size for this initial exploratory pilot study and to examine the effects of demographic and injury factors as potential covariates to inform design of future studies. In addition, most neurobehavioral measures selected for use in the study have age-specific forms spanning this age range. To ensure an adequate distribution across TBI severity and because disproportionately more children sustain complicated mild relative to moderate to severe TBI, we will stratify TBI recruitment into two severity groups (complicated mild vs. moderate/severe) and recruit consecutively within each group until we have at least 20% of the total sample in the moderate to severe TBI group. Children with OI were selected as a comparison group to control for premorbid risk factors for injury of any kind and to equate for the experience of having a traumatic injury and associated medical treatment (73, 74). In addition, comparing biomarkers between traumatically injured children with and without injury to the brain will help differentiate general injury effects on systemic biomarkers from those that are specific to brain injury (75). Children with spinal cord injury are excluded from both the TBI and OI groups to avoid confounding from neuroinflammation and brain involvement.

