### Data Reduction, Missing Data, and Attrition

Measures were selected that provide composites or summary indices representing each construct, reducing the need for substantial data reduction. Children will be eligible to remain in the study if at least one acute biosample (CSF, blood, or saliva) is obtained and both primary parent questionnaires (BRIEF-2/P, SDQ) are completed. This will reduce missing data on key variables and retain participants who refuse blood collection or are unable to produce sufficient saliva. In addition, statistical techniques such as mixed models, latent class trajectory analysis, and path analysis will be used, which estimate models based on all available data using maximum likelihood estimation (108). Consistent with previous studies in this population, we conservatively estimate that ~75% of participants will complete the follow-up visits (150 TBI; 75 OI) (2, 4, 5). Our power analyses account for this reduced participant sample size at follow-up.

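### Aim 1 fixes single-step Bonferroni although a difference is expected at every visit; Holm's step-down gives more power at the same familywise error

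*Protocol article*

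**What the plan says.** In the Protocol article, Statistical Methods and Power, Aim 1, methylation and protein are each compared between groups with a mixed effects ANOVA. The multiplicity rule is: "Alpha will be set at 0.05, and we will adjust for multiple comparisons using Bonferroni corrections". No step-down or other sequential version is mentioned, so the natural reading is the single-step rule, with every comparison tested at 0.05 divided by the number of comparisons.

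The same paragraph states "We expect a significant group × time interaction and group differences at each time point". The Aim 1 hypothesis at the end of the Introduction predicts higher methylation and lower protein "in children with TBI relative to OI at all time points". Measurements are taken "at three time points (acute, 6 months, 12 months) during the first year of recovery". That makes three between-group contrasts per biomarker, or six if the two biomarkers form one family.

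The only power statement for Aim 1 concerns the interaction: "We expect sufficient power (≥0.8) to detect even a small interaction effect". No power is given for the adjusted visit contrasts.

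**The concern.** The Aim 1 hypothesis is fully supported only if every visit contrast is significant. Single-step Bonferroni holds each contrast to the strictest threshold even after the others have been rejected. Its cost is therefore greatest when several null hypotheses are false, which is what this plan predicts.

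Holm's procedure applies the strict threshold only to the smallest p-value and relaxes it for each later one. It needs no added assumption, so for the accept/reject decision nothing is gained by staying with the single-step rule. What is at stake is a missed difference at 6 or 12 months, where fewer children are expected. The Introduction says the pilot's results will guide a larger multisite study, so such misses could carry over into that design.

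**Working it through.** **Inputs from the article**
- Alpha 0.05 (Aim 1); two-sided testing is assumed because sidedness is not stated.
- 200 TBI and 100 OI at enrolment (Study Overview).
- 150 TBI and 75 OI at follow-up (Data Reduction, Missing Data, and Attrition).
- Correlation 0.5 between repeated measures and partial η² = 0.01 (Aim 1).

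**Assumed:** the standardized difference d at each visit, since the article gives none. The range used is 0.2 to 0.6.

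**Step 1: the plan's own power figure.** For the interaction, f² = 0.01/0.99 = 0.0101. The noncentrality is λ = f² × N × m/(1 − ρ) = 0.0101 × 225 × 3/0.5 = 13.64, with 2 and 446 degrees of freedom. Power is 0.92, or 0.88 after multiplying λ by 8/9 for the 2:1 allocation. The stated figure of at least 0.8 is reproduced under G*Power's default effect-size definition. (Under its alternative SPSS-style definition power would be 0.46.) This figure says nothing about the visit contrasts.

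**Step 2: thresholds for three contrasts.** Bonferroni tests all three at 0.05/3 = 0.0167. Holm tests the ordered p-values at 0.05/3 = 0.0167, 0.05/2 = 0.025 and 0.05/1 = 0.05, stopping at the first failure.

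**Step 3: one contrast under Bonferroni, d = 0.4.** The mean of the z statistic is d/√(1/n₁ + 1/n₂).
- Acute: 0.4/√(1/200 + 1/100) = 0.4/0.1225 = 3.27. The critical value at 0.0167 two-sided is 2.39, so power = Φ(3.27 − 2.39) = 0.81.
- 6 or 12 months: 0.4/√(1/150 + 1/75) = 0.4/0.1414 = 2.83. Power = Φ(2.83 − 2.39) = 0.67.

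**Step 4: Bonferroni against Holm.** Correlated z statistics were simulated (300,000 draws, correlation 0.5 between visits, same group sizes).

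| d at acute / 6 / 12 months | All three significant: Bonferroni | Holm | 12-month contrast: Bonferroni | Holm |
|---|---|---|---|---|
| 0.2 / 0.2 / 0.2 | 0.04 | 0.09 | 0.16 | 0.20 |
| 0.3 / 0.3 / 0.3 | 0.18 | 0.32 | 0.39 | 0.47 |
| 0.4 / 0.4 / 0.4 | 0.47 | 0.65 | 0.67 | 0.76 |
| 0.5 / 0.5 / 0.5 | 0.77 | 0.88 | 0.87 | 0.93 |
| 0.6 / 0.6 / 0.6 | 0.94 | 0.98 | 0.97 | 0.99 |
| 0.5 / 0.4 / 0.3 | 0.33 | 0.50 | 0.39 | 0.53 |

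Averaged over the three visits at d = 0.4, power is (0.808 + 0.667 + 0.669)/3 = 0.71 with Bonferroni and (0.855 + 0.756 + 0.758)/3 = 0.79 with Holm.

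**Step 5: six contrasts in one family.** The chance that all six are significant at d = 0.4 is 0.13 with Bonferroni and 0.40 with Holm if the biomarkers are independent. It is 0.17 and 0.44 if a cross-biomarker correlation of 0.3 is assumed. At d = 0.5 with independence it is 0.46 and 0.78.

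**Step 6: error control.** With no true difference, the familywise error is 0.045 for both methods with three tests and 0.046 for both with six. With a true difference at the acute visit only (d = 0.4), Holm rejects each of the two true nulls with probability 0.024, so the familywise error is at most 0.024 + 0.024 = 0.048. In no scenario did Holm miss a rejection that Bonferroni made.

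**The case against.** Bonferroni is a valid procedure and nothing here inflates type I error, so the point concerns efficiency. That is correct. The chance of finding at least one difference is also the same under both methods (0.92 at d = 0.4, three tests), and the interaction test is untouched.

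The stronger objection concerns the scenario. A constant difference across visits implies no group × time interaction, yet the plan expects one, with the TBI group changing over time while OI stays stable. The groups may therefore converge. With d = 0.6/0.4/0.2 the chance of all three being significant is 0.15 against 0.27, and with 0.6/0.3/0.1 it is 0.04 against 0.09. Under steep convergence the prediction for every visit mostly fails whichever correction is used, because the late difference is small. This limits how much the change can deliver, but Holm still gains. Under milder convergence the gain is as large as with constant effects: 0.33 against 0.50 for 0.6/0.4/0.3.

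The family of comparisons is not defined in the article, and several methylation sites may be analysed, so the true family may be neither three nor six. Protein is measured in plasma, and children who refuse blood stay in the study, so the group sizes used are upper limits for protein. Both points affect the figures but not the ordering of the two methods.

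Finally, in a pilot the estimates and intervals matter, and Bonferroni has simple matching simultaneous intervals while Holm does not. This stands as a real but small cost. It is a reason to keep showing the intervals, not to keep the single-step decisions.

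**Conclusion.** The point holds. The plan names a valid rule that Holm's procedure dominates for the decisions it is meant to make, in the setting where the difference between the two matters. For three visits and a constant difference of 0.3 to 0.5 SD, Holm adds 0.11 to 0.18 to the chance of showing a difference at every visit, and about 0.06 to 0.09 to the power of each follow-up contrast. The gain is smaller if late differences are very small and larger if both biomarkers share one family. These sizes rest on assumed effects, the article's expected attrition and a visit correlation of 0.5. The dominance itself rests on none of them. This is avoidable loss of power on the aim's own prediction, worth correcting but not a threat to validity.

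**What to change.** In Statistical Methods and Power, Aim 1, replace the Bonferroni correction with Holm's step-down procedure at familywise alpha 0.05, over the same family of visit comparisons. Make the change before any group comparison is run.

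Bonferroni-adjusted confidence intervals may still be shown. The report should then note that such an interval can include zero for a contrast that Holm declares significant. That mismatch is the only cost: no extra children, samples or assumptions are needed, and the stated interaction power does not change.
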